### Control arm

At the baseline visit, nutrition counselors will provide participants randomized to the control group with an overview of the six principles of healthy eating based on the USDA MyPlate Plan [27]. Control participants will also receive a set of MyPlate healthy eating tip sheets by email shortly after the baseline visit which review these principles. We estimate that the USDA Daily Food Plan has the equivalent of four servings per day of the fruits and vegetables specified in our study.

### Study visits

Details on data collected each study visit are described in Table 2. Briefly, there will be four remote study visits: baseline (which occurs at about 6 weeks postpartum), 10 weeks, 20 weeks and at 52 weeks.

**Table 2 Tab2:** Primary outcome assessments

	Baseline	10 weeks	20 weeks	1 year
12 inflammatory markers	X	X	X	
DNA methylation	X	X	X	X
Maternal weight	X	X	X	X
Maternal weight circumference	X	X	X	X
Fruit and vegetable intake	X	X	X	X

### Primary outcome variables

Table 3 shows the primary outcome assessments, which are described in more detail below.

**Table 3 Tab3:** Grouping of fruits and vegetables for produce packing

Dark leafy greens	Collards, Kale, Mustard Greens, Romaine, Spinach, Swiss Chard
Lettuce	Butterhead, endive, leaf (red or green) lettuce
Deep orange/yellow fruit, roots or tubers	Apricot, cantaloupe, mango, nectarine, peach, papaya, butternut squash, carrot, Hubbard squash, pumpkin, sweet potato
Red fruit/vegetables	Cherries, pomegranate, watermelon, beets, red pepper, tomato
Citrus	Clementine, grapefruit (red/white), orange, tangerine
Cabbage family	Broccoli, Brussel sprouts, cabbage (green/red), cauliflower, Chinese broccoli, Chinese cabbage, bok choy
Allium	Garlic, leek, onion, scallion, shallot
Red/purple/blue berries	Cranberries, blackberries, blueberries, raspberries, strawberries
White (flesh)	Apple, pear, banana, cucumber, mushroom, crookneck (summer) squash, zucchini, parsnips, radish, turnip, jicama, rutabaga, potato
Unique fruit/vegetables	artichoke, fig, grapes, honeydew, kiwi, pineapple, plum, asparagus, avocado, celery, corn, eggplant, green pepper, okra, snap beans (green beans), snow peas

#### Inflammatory markers

We will use Mesoscale Discovery electrochemiluminescent sandwich assays to determine concentrations of 12 inflammatory markers in bilateral breastmilk samples collected at baseline and 20 weeks (adiponectin, leptin, c-reactive protein (CRP), interferon-γ (IFN-γ), interleukin-1β (IL-1β), interleukin-6 (IL-6), interleukin-8 (IL-8), tumor necrosis factor-α (TNF-α), basic fibroblast growth factor (bFGF), fms related receptor tyrosine kinase 1 (FLT1), placental growth factor (PlGF), vascular endothelial growth factor-D (VEGF-D) as described in a previous study [28].

#### DNA methylation

We will use the Infinium MethylationEPIC Kit (Illumina) to assess DNA methylation in epithelial cells from bilateral breastmilk samples collected at baseline and 20 weeks as described in a previous study [29].

#### Anthropometrics

Maternal and infant anthropometric measurements will be done at baseline, 10 weeks, 20 weeks and at 52 weeks as follows to accommodate COVID-19 pandemic-related contact restrictions.

#### Maternal weight

Weight in kilograms will be self-reported using a provided scale. Trained study personnel will guide participants in taking their weight measurement. Written instructions will be provided to each participant prior to the appointment. Measurements will be taken in duplicate and averaged.

#### Maternal waist circumference

Waist circumference in centimeters will be self-reported, using a provided tape measure. A video demonstrating appropriate measurement will be provided to the participant before the study visit. A trained study interviewer will guide the participant through the measurement. Measurements will be taken in duplicate and averaged.

#### Assessment of diet, including fruit and vegetable intake

Food intake will be collected using the Automated Self-Administered 24-h (ASA24) Dietary Assessment Tool [30], version ASA24-2020. Estimates of energy, nutrients, fruits and vegetables food group intake and portion size will be assessed using 24-h recall data collected at baseline, 10 weeks, 20 weeks, and 52 weeks. At each time point, two recalls will be obtained on weekdays and one recall on the weekend. For individuals who do not have computer access to high-speed internet, we will administer the ASA24 over the phone.

#### Potential covariates and modifiers

We will collect detailed information at the baseline visit on reproductive history, hormone use, prior pregnancies and breastfeeding practices, tobacco use and vaping, marijuana use, alcohol intake, weight, breast health, multivitamin and supplement use during pregnancy, and family history of breast and ovarian cancer. We will also collect updated information on physical activity, breastfeeding and infant feeding practices, medication and supplement use, and breast health.

### Secondary outcomes

#### Infant weight and length

The weight of the infant-mother dyad will be used to calculate infant weight. First, the mother will be instructed to weigh herself, after which she will be instructed to weigh herself while carrying her infant (lightly clothed with clean diaper). Infant weight will be calculated from the difference between mother plus infant weight minus maternal (only) weight. Measurement will be repeated and averaged.

Butcher paper will be used for measuring infant length. Ideally, the mother will have assistance in positioning the infant on the paper as instructed by the study personnel into a straight recumbent position. A line will be drawn on the paper at the position of the top of the head and at the bottom of the feet position. The length will be measured using the tape measure supplied to each participant. Measurement will be repeated and averaged.

#### Microbiome sample collections for future analyses

We will also collect, process and archive breastmilk, infant fecal specimens and maternal fecal specimens to allow us to examine the microbiome relevant to the health of the infant and mother in future analyses.

#### Changes in inflammatory markers and methylation profiles comparing the intervention arm to control arm

To conserve power for the DNA methylation analysis, we will analyze approximately the most variable 300 K DNA methylation profiles. Each inflammatory and methylation marker will be analyzed in separate linear mixed effects models with a random intercept to account for the within subject correlation of the repeated measurements obtained at baseline and 20 weeks. Prior to analysis, each marker will be natural logarithm transformed to satisfy normality assumptions. Each linear mixed effects model will be of the form: E(Y_ij_) = β_0_ + β_1_ x T_ij_ + β_2_ x G_i_ + β_3_ x G_i_ x T_ij_, where Y_ij_ denotes the CpG or inflammatory marker measurement for subject *i* at visit *j*, T_ij_ is the time (post randomization) for subject *i* at visit *j* and G_i_ denotes the randomization group for subject *i*. The primary hypothesis test of interest is H_0_: β_3_ = 0, testing the interaction of randomization group with time, using a likelihood ratio test. As a secondary analysis, we will also consider a linear model in which the baseline CpG level is included as an additional covariate. Missing data imputation methods will be considered to confirm the robustness of the findings. Adjustment for multiple comparisons will be based on the False Discovery Rate (FDR) procedure of Benjamini and Yekutiel [31], which allows for correlation between CpG or inflammatory marker levels. Threshold for statistical significance will be based on the raw p value that controls the rate of false discoveries to be under 5%. The adjustment for multiple testing will be carried out separately for the set of 300,000 CpG measurements and the set of 12 inflammatory markers.

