### Fruit and vegetable intervention arm

During the first 20 weeks of the intervention, participants will receive weekly produce boxes providing 32 servings of fruits and vegetables. The boxes will be comprised of 75% vegetables, with at least six servings of leafy greens. To encourage intake of variety of fruits and vegetables, a packing guide for produce boxes will be created based on nutrients and phytochemicals groupings developed by and Fisher (Table 1) [20]. At least one item from each category will be packed into the supplemental box of produce, which will be delivered to each participant along with recipes to assist in meal preparation. These boxes of fruits and vegetables will assist participants to transition from their pre-study diet and are intended to help the intervention participants achieve their goal of consuming 8 to 10 servings of fruits and vegetables, but not to supply their total fruit and vegetable intake or to restrict other produce intake. The produce box will contain a combination of fresh and frozen fruits and vegetables, providing participants with food preparation options. Participants will not be deterred from consuming canned produce, since research indicates canned and frozen fruits and vegetables are nutritionally sound alternatives to fresh produce [21–23]. The content of weekly boxes will be modified based on availability and study participant allergies.

**Table 1 Tab1:** Study activities at each assessment

	Pre-enrollment	Baseline	10 weeks	20 weeks	1 year
*Eligibility*					
Informed consent	X				
Eligibility Screener	X				
Fruit and vegetable screener	X				
*Randomization*					
Randomization		X			
Nutrition education session		X			
*Intervention arm only*					
Fruit and vegetable delivery (weekly for 20 weeks)		X	X	X	
Dietary counseling (weekly for 20 weeks then monthly up to 1 year)		X	X	X	
Three 24-Hour Diet Records (weekly for 20 weeks to guide counseling)		X	X	X	
Monthly counseling check-ins (between 20 weeks and one year)				X	X
*Anthropometrics*					
Maternal height	X	X			
Maternal weight	X	X	X	X	X
Maternal waist circumference		X	X	X	X
Infant length and weight		X	X	X	X
*Biological sample collection*					
Breastmilk specimen (if still breastfeeding)		X	X	X	X
Infant fecal specimen		X	X	X	X
Maternal fecal specimen (optional)		X		X	X
*Questionnaire data*					
Three 24 hour diet recalls (ASA24)		X	X	X	X
Breastfeeding Practices Questionnaire		X			
Breastfeeding Update Questionnaire			X	X	X

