### Power and sample size calculations

Power calculations for linear mixed models with adjustment for multiple testing were carried out through simulation studies. Due to computational considerations, adjustment for multiple testing was carried out through a conservative Bonferroni correction procedure to maintain the overall type I error at 0.05. CpG measurements (1a): In each dataset, we simulated repeated measurements of CpG levels according to a multivariate normal distribution with unit variance, assuming a within-subject correlation ρ, a mean difference in levels in the *control group* comparing baseline to the 20-week (T2) visit equal to 0.1 SD units and a mean difference in the intervention group between the 20-week (T2) and baseline (T0) of Δ SD units. The threshold for statistical significance was set at p = 0.05/300000, corresponding to a Bonferroni correction to maintain the overall Type I error at 0.05. When the correlation between the repeated CpG measurements is set to ρ = 0.5 (ρ = 0.3), a sample size of 200 per group results in 99% (82%) power to detect a mean difference in the intervention arm between baseline and T2 of Δ = 0.75 SD units, obtained by averaging over 100 simulated datasets. For the analysis of the 12 inflammatory markers, we simulated repeated measurements of inflammatory marker levels according to a multivariate normal distribution as described above. Assuming a Bonferroni correction to maintain the overall Type I error at 0.05 and when the correlation between the repeated inflammatory measurements is set to ρ = 0.5 (ρ = 0.3), a sample size of 200 per group results in 94% (84%) power to detect a mean difference in the intervention arm between baseline and T2 of Δ = 0.45 SD units, obtained by averaging over 100 simulated datasets.

Power calculations for the analyses of body weight, waist circumference and fruit and vegetable consumption at 1 year were based on a generalized linear model, using the R package pwr [32]. A sample size of 400 subjects results in 98% power to detect an effect size of 0.05 or larger, assuming a two-sided test and a type I error 0.05. We assumed the same variability at the two time points so the power is the same for 20 weeks and one year.

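### The random-intercept marker model assumes equal variance at baseline and 20 weeks; with 20-week milk missing, that assumption affects the primary test and can be dropped at no cost

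*Protocol article*

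**What the plan says.** In the protocol article's Data analysis section, the subsection on inflammatory markers and methylation profiles analyses each log-transformed marker on its own, using "linear mixed effects models with a random intercept to account for the within subject correlation of the repeated measurements"; the values analysed are those from baseline and 20 weeks. The mean model contains time, group and their product. The primary test is of β3 = 0, "testing the interaction of randomization group with time, using a likelihood ratio test". The text names neither a visit-specific variance nor a robust standard error. A linear model adjusting for baseline CpG level is secondary, and imputation is to be considered as a robustness check.

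On multiplicity the same subsection states: "Adjustment for multiple comparisons will be based on the False Discovery Rate (FDR) procedure" of Benjamini and Yekutieli, applied separately to the 300,000 CpGs and the 12 inflammatory markers.

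Table 1 (study activities) lists the milk collection as "Breastmilk specimen (if still breastfeeding", a condition that applies at 20 weeks. No expected rate of missing 20-week milk is given.

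The Power and sample size section simulates marker values "according to a multivariate normal distribution with unit variance", with 200 women per group and correlation 0.5 or 0.3. For the CpGs, "The threshold for statistical significance was set at p = 0.05/300000".

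**The concern.** A random intercept with a single residual variance is compound symmetry: one variance for both visits and one covariance. Here the visits fall at about 6 and 26 weeks postpartum, and the structure is applied to 12 markers and 300,000 CpG sites. The only figure bearing on it is the unit variance of the power simulation, which is a simulation setting and not evidence about the markers.

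The assumption matters once pairs are mixed with baseline-only women. The fit then borrows baseline variance to judge the 20-week mean. It also predicts the missing 20-week values from baseline with a slope that is wrong if the variances differ.

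Two things are at stake. One is the calibration of p-values read far out in the tail, where an error of a few per cent in a standard error is magnified. The other is bias in β3, if stopping breastfeeding is related to the baseline marker differently in the two arms. That bias arises even when data are missing at random, where a correctly specified likelihood would protect the estimate.

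**Working it through.** **The plan's own figures.** The plan gives no figure for this point. Its marker power assumes equal variances and 200 complete pairs per arm. At ρ = 0.5 the SD of change is √(2(1−0.5)) = 1 and the standard error of β3 is √(2/200) = 0.1. With z = 5.233 for 0.05/300000, a between-arm difference in change of 0.75 gives Φ(7.5 − 5.233) = 98.8%, against the stated 99%. Taking the text literally, with a net difference of 0.75 − 0.1 = 0.65, gives Φ(6.5 − 5.233) = 89.7%. That mismatch is a separate matter and does not bear on this point.

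**Inputs for the check.** From the article: two visits, 200 per arm, ρ = 0.5. Assumed: 20-week SD equal to s times baseline SD; a fraction m of 20-week samples missing completely at random, equally in both arms. Write p = 1 − m and set the baseline SD to 1.

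**Limiting fit.** The compound-symmetry variance v and correlation b minimise

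p/2·[2 ln v + ln(1−b²) + (1 + s² − 2bρs)/(v(1−b²))] + m/2·[ln v + 1/v].

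The fitted change in an arm is the 20-week mean of the pairs, minus b times (baseline mean of the pairs minus baseline mean of all women), minus the baseline mean of all women. With c = p + bm, its variance times the arm size is:

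- true: (s² − 2cρs + c²)/p + m(1−b)²
- model: v·[(1 − 2cb + c²)/p + m(1−b)²]

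**Complete pairs (m = 0).** Then c = 1, v = (1+s²)/2 and b = ρs/v. The model variance is 2v(1−b) = 1 + s² − 2ρs, which equals the true variance for any s. There is no error.

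**Worked case, s = 1.2, m = 0.35.** The fit gives v = 1.165 and b = 0.478, so c = 0.65 + 0.478 × 0.35 = 0.817.

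- True: (1.44 − 0.981 + 0.668)/0.65 + 0.35 × 0.522² = 1.734 + 0.095 = 1.829
- Model: 1.165 × [(1 − 0.782 + 0.668)/0.65 + 0.095] = 1.700
- Ratio of standard errors: √(1.700/1.829) = 0.964

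The error multiple is 2Φ(−z × ratio)/α. At 0.05/300000, z × ratio = 5.233 × 0.964 = 5.04, and the multiple is 2.7.

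| 20-week SD ratio (ρ = 0.5, 35% missing) | Model SE / true SE | ×error at 0.05 | ×error at 0.05/12 | ×error at 0.05/300000 |
|---|---|---|---|---|
| 0.8 | 1.045 | 0.81 | 0.66 | 0.27 |
| 1.0 | 1.000 | 1.0 | 1.0 | 1.0 |
| 1.1 | 0.981 | 1.09 | 1.2 | 1.7 |
| 1.2 | 0.964 | 1.18 | 1.4 | 2.7 |
| 1.5 | 0.923 | 1.41 | 2.0 | 8 |

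At 20% missing and ratio 1.2, the SE ratio is 0.981 and the CpG multiple 1.7. Changing ρ to 0.3 or 0.7 hardly alters the results.

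**Simulation of the likelihood ratio test** (2,500 datasets, 200 per arm, ρ = 0.5, 30% missing). The mean statistic, which should be 1, was 1.138 at ratio 1.5 (theory 1/0.936² = 1.141), 1.074 at 1.25, 0.954 at 0.75 and 0.998 at 1.0. With no missing data it was 1.009 at ratio 1.5 and 0.936 at 1.25. At ratio 1.5 and 35% missing, type I error at the 0.05 level was 6.5%, against 4.7% with an unstructured covariance.

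**Under the planned false discovery rule.** The Benjamini–Yekutieli constant is 13.19 for 300,000 tests, so the first-step cutoff is 0.05/(300000 × 13.19) = 1.26e-8. At 35% missing the actual per-test rate there is about 4.1e-8 (ratio 1.2) or 1.5e-7 (ratio 1.5). Both are below the Bonferroni rate of 1.67e-7. Over 300,000 true nulls that is about 0.012 and 0.045 expected false positives. In relative terms the multiples are larger at that cutoff, about 3.3 and 12.

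**Bias.** Suppose that in one arm only, stopping depends on the baseline marker. The bias is then about (ρs − b) times the baseline shift of women with a 20-week sample. With the fitted b above, ρs − b is 0.60 − 0.478 = 0.12 at ratio 1.2 and 0.75 − 0.434 = 0.32 at ratio 1.5. Simulated biases were about 0.04 and 0.10 SD, which corresponds to a shift of about a third of an SD. At ratio 1.5, type I error at the 0.05 level was 11.5% and 12.7% in two sets of runs, against 3.7% and 6.0% with unstructured covariance, where bias was about zero.

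**The case against.** The article fixes a random intercept and a mean model. It does not say in so many words that there is a single residual variance, and a full analysis plan could add visit-specific variances. That is fair, and it is why the point concerns the standard form of the stated model. Still, the covariance choice is stated rather than left open, and nothing in the text relaxes it.

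Both conditions for harm are assumed. Women enter already breastfeeding and have access to a lactation counselor, so missingness may be modest. Markers are log-transformed, which may even out the variances. The only variance figure is "multivariate normal distribution with unit variance". All of this stands: the documents do not show that either condition holds to any given degree.

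A reader might infer that missing milk alone makes the standard errors wrong, or that false CpG findings will multiply several-fold in the planned analysis. The documents support neither. With equal variances the error is exactly nil at any missing rate. With falling variance the test is conservative. The threshold 0.05/300000 belongs to the power calculation; the planned false discovery rule keeps the first-step rate below the Bonferroni rate in nearly every scenario tried, the exception being SD ratio 1.5 with 50% missing (about 3 times). That rule was adopted to allow for correlated tests, however. It takes the p-values as valid, its cutoff loosens as discoveries accrue, and it neither restores lost power nor removes bias.

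The secondary baseline-adjusted model needs no equality of variance across visits and could expose a discrepancy, as could imputation. Neither is the primary test, and the secondary model is described for CpGs only.

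**Conclusion.** The point holds as a conditional one. The stated model carries an equal-variance assumption that the plan does not support, and the design produces the missing 20-week values under which the assumption starts to matter. The size depends on a missing rate and a variance ratio that the documents do not give. A 10% difference in SD is a minor matter. A several-fold change in CpG error needs roughly an SD ratio of 1.25 with 30% missing, or 1.5 with 20%. For the 12 inflammatory markers the standard-error effect is modest. The bias is the more serious possibility for those markers, because it disturbs even the 0.05 level, but it also requires arm-specific dependence of stopping on the baseline marker. This is a free improvement, not a demonstrated error in the plan.

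**What to change.** In the Data analysis subsection on inflammatory markers and methylation profiles, replace the random intercept with an unstructured 2x2 within-woman covariance: separate variances at baseline and 20 weeks, and their covariance. Keep the mean model and the likelihood ratio test of β3 unchanged. Keeping the random intercept and allowing visit-specific residual variances amounts to the same model, provided the covariance is neither negative nor larger than either variance.

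The cost is one more variance parameter per model. No new data are needed. With complete pairs the test is identical, because both models then reduce to comparing within-woman changes, so no power is given up. Use the same structure if the marker power figures are re-run.

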#### Changes in maternal body weight and body fat distribution comparing the intervention arm to control arm at 20 weeks

Separate multivariate linear regression models will be fit to analyze the effect of randomization group on body weight or body fat distribution (waist circumference) at the end of intervention at 20 weeks. Body weight or waist circumference at 20 weeks will be considered as the outcome, with independent covariates including baseline weight or waist circumference, randomization group and other potential confounders. The distributions of body weight and waist circumference will be examined graphically and appropriate transformations (e.g., natural logarithm) will be considered. The statistical significance of the effect of randomization group on outcome will be assessed through a likelihood ratio test.

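### The primary test for CpGs and inflammatory markers is, with complete data, an unadjusted change-score contrast; baseline adjustment is secondary and named only for CpGs, which costs precision at the planning correlations

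*Protocol article*

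**What the plan says.** All places are in the protocol article.

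- **Marker model** (Data analysis, inflammatory markers and methylation profiles). Each log-transformed marker gets its own random-intercept model, to handle the "within subject correlation of the repeated measurements obtained at baseline and 20 weeks". Besides intercept and time, the mean contains "β_2_ x G_i_ + β_3_ x G_i_ x T_ij", so the arms may differ freely at baseline.
- **Primary test** (same section). "The primary hypothesis test of interest is H_0_: β_3_ = 0, testing the interaction of randomization group with time, using a likelihood ratio test".
- **Baseline adjustment** (same section). "As a secondary analysis, we will also consider a linear model in which the baseline CpG level is included as an additional covariate". The sentence names CpGs; nothing comparable is stated for the 12 inflammatory markers.
- **Weight and waist at 20 weeks** (next section). The main analysis is a regression of the 20-week value, "with independent covariates including baseline weight or waist circumference, randomization group and other potential confounders". The 1-year section carries the same approach forward.
- **Randomization section.** Arms are assigned after the baseline visit.
- **Power section.** Unit variance at each visit, within-subject correlation ρ of 0.5 (alternative 0.3), 200 per arm and Bonferroni thresholds; for CpGs, "The threshold for statistical significance was set at p = 0.05/300000".

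**The concern.** Because randomization follows the baseline visit, the true arm difference at baseline is zero by design. A model that estimates this difference freely and then tests the change spends information on a quantity already known. Baseline adjustment avoids that. The gain is largest when the correlation between visits is modest, and the protocol plans for modest correlations.

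The biomarkers also face the heaviest multiplicity burden in the trial (300,000 CpGs and 12 markers), yet they get the less precise method, while weight and waist get the better one. At stake is power for the biomarker outcomes, from data that will be collected anyway.

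**Working it through.** **Inputs** (Power section unless noted). n = 200 per arm; SD = 1 at both visits; ρ = 0.5 or 0.3; control change 0.1 SD; intervention change Δ = 0.75 SD (CpG) or 0.45 SD (inflammatory). Thresholds: 0.05/300000 = 1.67×10⁻⁷ (two-sided critical value 5.233) and 0.05/12 = 0.00417 (critical value 2.865). I take one value per woman per visit, as the model's subject and visit indices imply, and the same follow-up time for all women.

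**Step 1: what the planned test is.** With two visits, complete data and free time, group and group-by-time terms, β3 is the between-arm difference in mean change. Its per-woman variance is 1 + 1 − 2ρ = 2(1 − ρ), so

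SE(change) = √[2 × 2(1 − ρ)/200] = 0.1000 at ρ = 0.5 and 0.1183 at ρ = 0.3.

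**Step 2: baseline-adjusted analysis.** The per-woman variance is 1 − ρ², so

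SE(adjusted) = √[2(1 − ρ²)/200] = 0.0866 at ρ = 0.5 and 0.0954 at ρ = 0.3.

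**Step 3: reproduce the stated power.** Power = Φ(d/SE − critical value), where d is the net between-arm difference in change. The article states 99% (82%) for CpGs and 94% (84%) for inflammatory markers, at ρ = 0.5 (0.3).

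- Taking Δ itself as d, with the change-score SE: CpG 98.8% (86.6%; 84.1% by noncentral t, 84.0% by simulated likelihood ratio test); inflammatory 94.9% (82.6%). Three figures agree within 2 points. CpG at ρ = 0.3 is about 2 points off by t or likelihood ratio, which is inside the error of 100 simulated datasets (√[0.82 × 0.18/100] ≈ 3.8 points).
- Taking d = Δ − 0.1, as the text literally describes: CpG 89.7% (60.3%); inflammatory 73.7% (53.7%). None agrees.

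The adjusted variance does not reproduce the four figures under either reading. The stated power therefore fits the change-score contrast with Δ as the net difference. Both readings are carried below.

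**Step 4: relative efficiency.** (1 − ρ²)/[2(1 − ρ)] = (1 + ρ)/2.

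| ρ | efficiency | information lost | per arm for the planned test to match adjustment with 200 |
|---|---|---|---|
| 0.3 | 0.65 | 35% | 200/0.65 = 308 |
| 0.5 | 0.75 | 25% | 200/0.75 = 267 |
| 0.7 | 0.85 | 15% | 235 |
| 0.9 | 0.95 | 5% | 211 |

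For comparison, ignoring baseline and comparing 20-week values has per-woman variance 1.0. The change contrast has 1.0 at ρ = 0.5 and 1.4 at ρ = 0.3, so over the planned range it gains nothing from the baseline sample.

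**Step 5: power, planned test to baseline-adjusted** (normal approximation, 200 per arm).

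| outcome | d (SD) | ρ = 0.5 | ρ = 0.3 |
|---|---|---|---|
| Inflammatory, 0.1 subtracted | 0.35 | 73.7% to 88.0% | 53.7% to 78.9% |
| CpG, 0.1 subtracted | 0.65 | 89.7% to 98.8% | 60.3% to 94.3% |
| Inflammatory, Δ as net | 0.45 | 94.9% to 99.0% | 82.6% to 96.8% |
| CpG, Δ as net | 0.75 | 98.8% to >99.9% | 84–87% to 99.6% |

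Example (first row, ρ = 0.5): 0.35/0.1000 − 2.865 = 0.635, Φ = 0.737; 0.35/0.0866 − 2.865 = 1.176, Φ = 0.880.

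**Step 6: missing 20-week milk.** Milk is collected only while breastfeeding continues, and no rate is given. Assuming 20% (40%) of 20-week samples missing at random, the loss is 21–30% (17–24%) over ρ = 0.5 to 0.3.

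**Step 7: is deleting β2 enough?** A random intercept alone forces equal variance at the two visits. The article gives no visit-specific SDs, so assume a 20-week SD of 1.2 times baseline and ρ = 0.5. The fitted common variance is (1 + 1.44)/2 = 1.22 and the covariance 0.60, so the working correlation is 0.60/1.22 = 0.492. The true variance of the constrained contrast is 1.44 + 0.492² − 2 × 0.492 × 0.60 = 1.092; the model reports 1.22 × (1 − 0.492²) = 0.925. The true SE is √(1.092/0.925) = 1.09 times the reported one, and a nominal 5% test runs at 7.1%. At an SD ratio of 1.5 the factor is 1.18 and the rate 9.6%. At 0.8 the test is conservative.

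**The case against.** The strongest defence is that nothing here is an error. The biomarker outcome is defined as change from randomization to 20 weeks, and "testing the interaction of randomization group with time, using a likelihood ratio test" is a standard, unbiased way to assess it. The power section fits the same contrast, so design and test agree, and a baseline-adjusted check is already foreseen for CpGs. All of this stands. The point concerns efficiency, not validity, and a reader who infers that the planned test is biased or inflates false positives would be wrong: with free β2 it reduces to the change-score test and stays valid even if variances differ between visits.

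Three further limits also stand.

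- A reader might take 25–35% as a fixed loss. It holds at the planning correlations, with equal variances and complete data; the article reports no observed correlation for these markers.
- A reader might conclude that the biomarkers are underpowered and that adjustment restores most of what they lack. That rests on subtracting the 0.1 SD control change. Under the reading that fits the published figures, little power is missing at ρ = 0.5.
- A reader might think it enough to strike β2 from the model. Step 7 shows that this makes the SE depend on equal visit variances. Nor is the constrained model interchangeable with ANCOVA when samples are missing: ANCOVA drops women with only one sample, the constrained model keeps them. The present mixed model keeps them too, so that is no gain over it.

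None of this is a reason to prefer the change contrast as primary. With equal variances, adjustment is never less precise in large samples, whatever ρ is.

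**Conclusion.** The concern holds as a matter of efficiency. The article fixes an unadjusted change contrast as primary for CpGs and inflammatory markers, and leaves the more precise analysis as a secondary option for CpGs alone, although it uses that analysis for weight and waist. The loss is 25% at ρ = 0.5 and 35% at ρ = 0.3, smaller at higher correlations and somewhat smaller with missing 20-week samples.

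The power gain depends on how Δ is read: 14 to 34 points if the control change is subtracted, except 9 points for CpGs at ρ = 0.5; or 1 to 4 points at ρ = 0.5 and roughly 13 to 16 points at ρ = 0.3 if Δ is the net difference. These figures use the power section's Bonferroni thresholds, not the false discovery rate procedure planned for the analysis; the relative efficiency does not depend on the threshold.

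The change should be made, but the trial's validity does not hang on it.

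**What to change.** Make the baseline-adjusted analysis primary for CpGs and all 12 inflammatory markers: regress the log 20-week value on arm and log baseline value, and test the arm coefficient.

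Alternatively, use a mixed model with a common baseline mean (β2 = 0) and an unstructured two-visit covariance. This also keeps women with only one sample. Do not merely delete β2 from the random-intercept model.

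Keep the present model as a sensitivity analysis, and restate the power for the new primary test, saying whether Δ is net of the control change.

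The cost is a rewrite of the model paragraph and a rerun of the power calculation, settled before any unblinded analysis. No further data or participants are needed.
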